### Interim analyses {21b}

No interim analyses will be planned.

### Methods for additional analyses (e.g., subgroup analyses) {20b}

No subgroup analysis will be conducted.

### Methods in analysis to handle protocol non-adherence and any statistical methods to handle missing data {20c}

To mitigate protocol non-adherence, participant education will place significant emphasis on the importance of adhering to the protocol. Meanwhile, investigators and research staff will receive comprehensive training and ongoing support. Furthermore, a WeChat group will be established for each participant. Within this group, daily treatment photos will be shared to facilitate supervision and identification of stimulation sites.

We anticipate minimal missing data in the outcome (rating scale) assessments, as we have provisions in place to assess participants remotely using a dedicated mobile application in the event that they are unable to visit the hospital during the treatment phase. Missing data will be imputed using the last observation carried forward (LOCF) analysis.

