#### Sample size and power {14}

The sample size and power calculations were centered on the primary outcomes, which pertained to the alterations in UPDRS III scores from the baseline assessment to the 4-month follow-up assessment after 4 months of LIPUS treatment. In accordance with the findings derived from the limited sample study involving 20 patients, the LIPUS group exhibited a mean change of 5.54 ± 8.03, while the sham group showed a mean change of − 0.71 ± 2.25. The researcher utilized the sample size calculation software PASS to compute the sample size for each group, which was *n*_1_ = *n*_2_ = 21 (1:1 allocation ratio), to detect differences with a two-sided significance level of 0.05 and 90% power calculations. With the consideration of a 10% dropout rate, the final sample size is expected to be 48. In the prior investigation [36], wherein a clinically meaningful alteration in UPDRS III scores was established as a 5-point disparity, the study determined that the efficiency of the existing sample size in power calculations reached 0.8078.

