## Data collection and management

### Plans for assessment and collection of outcomes {18a}

The primary outcome data will be evaluated at baseline, after 2 months of treatment, and after 4 months of treatment. Secondary outcomes, which encompass additional rating scales and hdEEG, will likewise be assessed at baseline, after 2 months of treatment, and after 4 months of treatment. Furthermore, secondary outcomes, such as fMRI, will be acquired at the baseline and upon completion of the treatment. All variables outlined in the protocol will be meticulously recorded within an encrypted Microsoft Office Excel document. The investigators responsible for data entry in this Office Excel file hold the duty of upholding data accuracy and completeness. To supervise and administer the trial data, a management team has been established, composed of the principal investigator, senior investigator, a research assistant, and a doctorate student each with their respective responsibilities for tasks.

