### Plans to promote participant retention and complete follow-up {18b}

Patients will be required to participate in all evaluations and treatments over the course of the 4-month trial. The patients will be provided with trial-related assessments, such as rating scales and medical examinations, which will include ultrasound examinations, hdEEG, and fMRI, without incurring any financial expenses or burdens.

If a participant chooses to discontinue their involvement in the study during the therapy phase and fails to complete the entire 4-month treatment duration, their data will not be maintained for the purpose of analysis. It is imperative to exert all conceivable efforts in order to incentivize and provide assistance to patients, ensuring their sustained participation in the study until the completion of their intended outcome assessments.

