### Data management {19}

Clinical data will be collected and managed using an electronic database during participants’ hospital visits at baseline, 2 months, and 4 months (Table 1). The paper version materials, which include the protocol, case reported forms, informed consent forms, and electronic version database, will be kept in an independently secured box at Shanghai Sixth People’s Hospital by the principal investigator. The research assistants will send out reminder emails and make phone calls to ensure that participants complete the research. If (1) the participant withdraws his or her consent and (2) exclusion criteria are discovered after registration, the participant will be removed from the study. The reason for the suspension as well as the date of the suspension will be documented. The consent form will include permission to utilize data collected prior to the participant’s withdrawal.

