## Statistical methods

### Statistical methods for primary and secondary outcomes {20a}

SPSS 26.0 will be used for the statistical analysis. Continuous variables will be represented by a mean and standard deviation, whereas categorical variables will be represented by counts and percentages. The intention-to-treat principle will be used to analyze the UPDRS III score (primary outcome) [37], which will include data from all randomized individuals. A per-protocol analysis of other outcomes from the participants who completed the entire research will also be performed. Multiple imputations will be used to replace missing data using multivariable regression models with chained equations. The mean treatment differences and 95% CIs between measures with LIPUS and sham-LIPUS will be computed. All statistical tests will be two-sided with a *p* < 0.05 statistical significance level.

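### The protocol gives three incompatible rules for missing or discontinued participants' data (multiple imputation, LOCF, exclusion), so the primary UPDRS III analysis is not uniquely defined

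*Protocol article*

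**What the plan says.** The protocol article deals with missing outcome data in four places.

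- **Statistical methods for primary and secondary outcomes {20a}.** "The intention-to-treat principle will be used to analyze the UPDRS III score (primary outcome"), with all randomized individuals included. The same paragraph says: "Multiple imputations will be used to replace missing data using multivariable regression models with chained equations".
- **Handling of non-adherence and missing data {20c}.** "We anticipate minimal missing data in the outcome (rating scale) assessments", because remote assessment by mobile application is available. It then says: "Missing data will be imputed using the last observation carried forward (LOCF) analysis".
- **Participant retention {18b}.** For a participant who chooses to leave during therapy and does not complete the 4 months, "their data will not be maintained for the purpose of analysis".
- **Data management {19}.** The consent form is to include "permission to utilize data collected prior to" withdrawal.

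Item {18a} sets the visits: "The primary outcome data will be evaluated at baseline, after 2 months of treatment, and after 4 months of treatment". The sample size section {14} allows for 10% dropout in a total of 48.

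**The concern.** An intention-to-treat analysis of everyone randomized needs one stated rule for a participant with no 4-month score. The article gives two imputation rules with no ranking and no split by outcome. For a participant who leaves therapy early it gives a third rule, which removes the data altogether. Three analysts following different sentences would produce three primary results, and each could say that the protocol was followed.

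What is at stake is chiefly that the primary result is fixed in advance. With 48 participants and 10% expected dropout, about five people would be handled differently under each rule, enough to move a borderline p value. The second issue is quality. LOCF enters a baseline or 2-month score as if it had been measured at 4 months and carries no uncertainty for having done so. Multiple imputation is designed to avoid that. The exclusion in {18b} also undermines multiple imputation itself, because it would discard the 2-month scores that the imputation model most needs.

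**Working it through.** **Do the rules differ only in scope?** Item {20a} places multiple imputation straight after the intention-to-treat analysis of UPDRS III. Item {20c} places LOCF straight after a sentence on rating-scale assessments, and UPDRS III is a rating scale. Both therefore reach the primary outcome. No sentence calls either one primary, secondary or sensitivity. Wording alone cannot reconcile them.

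**Does {18b} fit either rule?** No. If an early leaver's data are not analysed, there is no score to carry forward and no 2-month score to impute from, and the analysis set is no longer all randomized participants. At 10% dropout, 0.10 × 48 = 4.8, so about five people would be removed. Item {19} asks consent for earlier data to be used, which has little purpose if {18b} then excludes them.

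**Planning figures from {14}, reproduced first.** "the LIPUS group exhibited a mean change of 5.54 ± 8.03"; the sham change is −0.71 ± 2.25. The difference is 5.54 − (−0.71) = 6.25. A Welch t-test at two-sided 0.05 gives power 0.893 with 20 per arm and 0.908 with 21, so 21 is the smallest n that reaches 90%. Then 21 / 0.9 = 23.3, rounded up to 24 per arm, or 48. At 24 per arm and 5 points, power is 0.8078. All match the article, and none is disputed here.

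**Size of the LOCF effect.** Assumptions not in the article: a positive change means improvement; a share *f* of each arm's 4-month change is present at month 2; dropout is unrelated to outcome. With a fraction *p* missing in an arm, the expected LOCF mean is

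(1 − *p*) × change + *p* × (carried change),

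where the carried change is *f* × change from month 2 and 0 from baseline.

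Per participant, with *f* = 0.5 (linear accrual):

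- LIPUS: 5.54 − 2.77 = 2.77 points too little from month 2; 5.54 from baseline.
- Sham: 0.355 points of worsening hidden from month 2; 0.71 from baseline.

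Effect on the difference at 10% missing:

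- Both arms, from month 2: 0.10 × (2.77 + 0.355) = 0.31, leaving 5.94 (−5%).
- Both arms, from baseline: 0.10 × (5.54 + 0.71) = 0.63, leaving about 5.63 (−10%).
- LIPUS only: 0.10 × 2.77 = 0.28 from month 2; 0.10 × 5.54 = 0.55 from baseline.

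At 20% missing in both arms the difference is 5.63 (from month 2) or 5.00 (from baseline).

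With *f* = 1 (effect complete by month 2) and dropout after month 2, the shrinkage is 0.

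**The direction can reverse.** Suppose there is no treatment effect, both arms worsen linearly by 3 points, and 20% leave the LIPUS arm only, after month 2. The LIPUS mean under LOCF is 0.8 × (−3) + 0.2 × (−1.5) = −2.70, against −3.00 in sham: a spurious benefit of 0.30.

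**How often would the choice matter?** A simulation used 24 per arm, the article's SDs, *f* = 0.5, correlation 0.7 between month-2 and month-4 changes, random dropout after month 2 and 1,500 replicates. At a true difference of 6.25, LOCF averaged 5.88 and multiple imputation 6.20 with 10% dropout, and 5.61 and 6.25 with 20%. The two rules fell on opposite sides of p = 0.05 in 1.3% and 3.1% of trials; at a true difference of 5 points, in 3.6% and 5.3%. These rates depend on how the imputation model is set up and should be read as a few in a hundred.

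**The case against.** **The effect is small and may be absent.** The article expects little missing data and provides remote assessment. With equal dropout the LOCF shrinkage is 0 to 10% at 10% missing, and it goes against LIPUS. This stands, and the point should not be presented as a large bias.

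**Blinding limits selective choice.** Items {17a} and {17b} keep analysts blinded and reveal the groups only after the primary and secondary analyses. This limits choosing by direction. It does not stop an analyst from computing coded results under both rules and keeping the smaller p value.

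**LOCF might be meant for rating scales and multiple imputation for the rest.** This is possible, but the article does not say so, and {20a} introduces multiple imputation directly after the UPDRS III analysis.

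**A full protocol or analysis plan may settle it.** A later document could only overrule a sentence already published. This is a stated conflict, not a detail left out.

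**Stronger readings that the article does not support.** A reader might infer that the effect is expected to build up over 4 months, so that LOCF must be biased. No section gives a trajectory or a 2-month pilot value. The introduction's remark that symptoms worsen describes the disease course, not two months on stable medication; the pilot sham change is only −0.71. A reader might also infer that LOCF understates the standard error by about 5%, from √(43.2/48) = 0.949. That assumes carried values vary like observed 4-month changes, whereas a carried baseline gives a change of exactly zero. It is a rough illustration only.

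**Conclusion.** The contradiction is plain and concerns the primary analysis. {20a} and {20c} name different imputation methods without ranking or scope, and {18b} removes early leavers against the all-randomized analysis in {20a} and out of keeping with the consent provision in {19}. The primary UPDRS III result is therefore not uniquely defined.

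That finding needs no assumption. The numerical size does: with linear accrual and 10% missing in both arms, LOCF takes 0.31 to 0.63 off a 6.25-point difference (0.28 to 0.55 if only LIPUS participants are lost). It takes nothing off if the effect is complete by month 2 and dropout follows, and unequal dropout can bias it either way. Multiple imputation is not free of assumptions either: it is unbiased only if data are missing at random and the model is right. It is preferred because it uses the 2-month score without treating it as the 4-month result, and because it carries the uncertainty of the missing value.

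The correction is needed because the primary rule is undefined. The documents show neither a large bias nor an intention to choose between results.

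**What to change.** 1. In {20a}, name multiple imputation by chained equations, with baseline and 2-month UPDRS III and treatment arm in the model, in all randomized participants, as the only primary rule.
2. In {20c}, delete the LOCF sentence or label it a sensitivity analysis.
3. In {18b}, state that data collected before discontinuation are kept in the primary analysis where consent allows, in line with {19}.
4. Optional: one sensitivity analysis that shifts imputed LIPUS values towards no benefit.

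Date the decision before unblinding. Because {17b} reveals the groups only after the analyses, it should also precede any between-group comparison, coded or not. The article gives February 2024 as the expected last visit, so this is pressing. A mixed model for repeated measures would also be acceptable as the primary rule; what matters is that exactly one is named.

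Cost: a few sentences and a little analysis work, through the amendment route in {25}. No new data are needed and the sample size does not change.

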### Plans to give access to the full protocol, participant-level data, and statistical code {31c}

Anonymized participant data may be provided by the corresponding author upon reasonable request. However, it should be noted that there are no plans to grant public access to participant data and the statistical code.

## Oversight and monitoring

### Composition of the coordinating center and trial steering committee {5d}

The management group responsible for conducting clinical monitoring activities will consist of several members, including the principal investigator, senior investigator, a research assistant, and a doctorate student, which will meet on a monthly frequency. It is important to highlight that the present study does not incorporate a trial steering group.

### Composition of the data monitoring committee, its role, and reporting structure {21a}

This trial does not have a formal data monitoring committee in place, as there are no interim analyses planned, and there are no procedures for early stopping.

### Adverse events reporting and harms {22}

From the start of the trial (either LIPUS or sham treatment) to the 4-month follow-up visit, the primary safety endpoint is the occurrence of adverse events. The primary outcome is a four-month safety visit. Meanwhile, research visits will be scheduled every two months. Adverse events will be assessed using the following criteria: those reported spontaneously by participants, those reported in response to a particular inquiry for adverse events, and those noticed by the neurologists during the general and neurological examinations at each visit. All adverse events that occur throughout the trial will be meticulously documented.

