**Methods:**

This protocol is a single-site, prospective, double-blind, randomized controlled trial (RCT). Forty-eight participants with clinically confirmed PD will be randomly allocated to one of two groups: LIPUS group or sham group. All of the participants continue to use pharmacological therapy as a fundamental treatment. The primary outcome is the difference between groups from baseline to 4 months in the change in the Unified Parkinson’s Disease Rating Scale (UPDRS) motor score (part III). The secondary outcomes include the rating scales such as the Mini-Mental State Examination (MMSE), and other three rating scales, and medical examinations including high-density electroencephalography (hdEEG) and functional magnetic resonance imaging (fMRI). The primary safety outcome will be assessed at 4 months, and adverse events will be recorded.

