### Criteria for discontinuing or modifying allocated interventions {11b}

In this study, the criteria for discontinuing the intervention will be (1) participants who are unable to complete the clinical study, (2) participants who voluntarily withdrew informed consent, and (3) participants who experience serious adverse events. As of now, no adverse events have been reported during the course of LIPUS treatment.

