### Outcomes {12}

#### Primary outcome

The primary effectiveness outcome will be the difference in mean change (at baseline, 2 months, and 4 months) across groups (LIPUS vs sham treatment) according to blinded site evaluation of the UPDRS III score for the affected side. The primary outcome is calculated as the sum of the unilateral items for the following: speech, facies, tremor in resting, intentional tremor, rigidity, rapid movements of the fingers, rapid hand movements, alternating movements, leg movements, getting up from a chair, posture, posture stability, starting walking, and bradykinesia in the third section (motor). The scoring system includes the following: 0 points = no involvement; 1 = detectable disorders; 2 = moderate disorders; 3 = considerable disorders; 4 = no function or severe disorders [29]. Therefore, the primary endpoint score ranges from 0 to 56, with higher scores suggesting worse parkinsonism.

Meanwhile, Fahn and Elton created the Unified Parkinson’s Disease Rating Scale (UPDRS), which is made up of six elements. These are as follows: (I) the state of intellectual and mood disorders; (II) activities of daily living (separately for phase “on” and “off”); (III) motor examination; (IV) complications of treatment; (V) stages of the disease; (VI) self-assessment of independence using the Schwab and England Scale. Furthermore, the subjective, patient-derived Activities of Daily Living (Part II) component of the UPDRS corresponds well with the objective, physician-derived motor section (Part III) [30].

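### The primary safety endpoint is given both as adverse events over 4 months and as a visit called the primary outcome, and the analysis rules, read literally, can leave out harms in participants who stop early

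*Protocol article*

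**What the plan says.** All references are to the protocol article.

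- **Adverse events reporting and harms {22}** sets a cumulative window, starting with treatment and running "to the 4-month follow-up visit, the primary safety endpoint is the occurrence of adverse events". The next sentence is "The primary outcome is a four-month safety visit". The section closes with "All adverse events that occur throughout the trial will be meticulously documented".
- **Abstract, Methods** names the UPDRS motor score as the primary outcome and then says "The primary safety outcome will be assessed at 4 months, and adverse events will be recorded".
- **Primary outcome {12}** begins "The primary effectiveness outcome will be the difference in mean change (at baseline, 2 months, and 4 months) across groups" and concerns the UPDRS III score.
- **Criteria for discontinuing or modifying allocated interventions {11b}** lists "participants who experience serious adverse events" among the grounds for ending the intervention.
- **Plans to promote participant retention and complete follow-up {18b}** says that the data of a participant who chooses to leave during therapy, and so does not finish 4 months of treatment, will not be kept for analysis.
- **Data management {19}** says that the consent form will allow use of data gathered before withdrawal.
- **Statistical methods for primary and secondary outcomes {20a}** applies intention-to-treat to UPDRS III and adds a per-protocol analysis of the other outcomes in those who completed the study.

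**The concern.** Two things are wrong. First, consecutive sentences in item 22 give a proper safety endpoint and then a visit labelled as the primary outcome. The label conflicts with the definition just before it, and with UPDRS III as the primary outcome in the abstract and item 12. The abstract does not settle the matter, because it mentions the safety outcome at 4 months and the recording of adverse events as separate items.

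Second, the rules on whose data are analysed do not secure a count in everyone exposed. A participant who leaves because of an adverse event fits the wording of the item 18b exclusion, and the only population that item 20a names for outcomes other than UPDRS III is completers. Harms that lead people to stop are those a safety endpoint most needs to count. The Introduction describes this as the first clinical trial of the team's own wearable device in Parkinson's disease. Treatment is self-administered at home every day, and the trial has no formal data monitoring committee. With 24 participants per arm, leaving out one or two people with an event could change the safety summary.

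**Working it through.** The protocol states no figure for the safety endpoint, so there is none to reproduce. The check compares the sections, followed by an illustration under stated assumptions.

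**1. What is the endpoint?** Item 22 gives a variable (occurrence of adverse events) and a window (start of treatment to 4 months). Its next sentence gives only an occasion. An occasion cannot be tabulated by arm, so the sentence cannot serve as a definition. It also gives the trial a second primary outcome beside UPDRS III. The abstract's wording fits either a cumulative count evaluated at month 4 or a status read at month 4.

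**2. Are events collected?** Yes, on the text. Item 22 takes spontaneous reports, answers to a specific inquiry, and "those noticed by the neurologists during the general and neurological examinations at each visit", and it promises to document every event in the trial.

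**3. Are collected events counted?** The text does not ensure this.

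| Section | Effect on an early leaver's safety data |
|---|---|
| Item 22, definition and closing sentence | counted |
| Item 22, visit sentence | unclear; excluded if only visit attenders count |
| Item 18b | excluded if the participant chose to leave before 4 months |
| Item 20a | no intention-to-treat rule outside UPDRS III; completers named for other outcomes |
| Item 19 | use of data from before withdrawal is permitted |

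These rows do not agree. Documenting an event does not place it in the endpoint.

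**4. What could the difference be?** The total is 48, so there are 48/2 = 24 per arm. The calculation required 21 per arm before the dropout allowance, so the plan itself provides for 24 − 21 = 3 non-completers per arm. Suppose *k* participants in an arm have an adverse event and leave before month 4, and *x* completers have an event. Assume also that nobody else leaves.

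- Count in all users: (*x* + *k*)/24
- Count in completers: *x*/(24 − *k*)

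With *x* = 0 (assumed):

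| *k* (assumed) | All users | Completers |
|---|---|---|
| 0 | 0/24 = 0% | 0/24 = 0% |
| 1 | 1/24 = 4.2% | 0/23 = 0% |
| 2 | 2/24 = 8.3% | 0/22 = 0% |
| 3 | 3/24 = 12.5% | 0/21 = 0% |

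**5. Which arm would it favour?** That depends on *k* in each arm. With *x* = 0 in both arms, *k* = 3 on LIPUS and 0 on sham would hide an excess of 12.5 percentage points on LIPUS. The reverse would hide an excess of 12.5 points on sham. Equal *k* leaves the difference between arms at zero and understates the rate in both. The documents do not say which case applies.

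**The case against.** The strongest reply is that item 22 already defines the endpoint cumulatively and promises to document all events. One badly formed sentence should not override the clear text around it, and the natural reading is that month 4 is the main time for evaluating safety. The abstract, a one-line condensation, fits that reading. This stands as regards collection: the visit sentence alone does not lose events.

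A reader might infer more than the documents support:

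- **That participants stopped for a serious event drop out of the endpoint.** Item 11b ends the intervention; it does not end follow-up or event recording. Item 18b is worded for those who choose to leave, and it also urges every effort to keep patients in until their assessments are complete.
- **That the error favours LIPUS.** This needs more event-related stopping on LIPUS than on sham. No such rate is given, and item 11b reports no adverse events during LIPUS treatment so far.
- **That active inquiry happens only every two months.** Item 22 attaches the visits to the neurologists' examinations. It gives no interval for the inquiry and no visit restriction on spontaneous reports.

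It can also be said that a safety population is usually left to the analysis plan. That is fair for a plan that is silent. Here the article states an exclusion rule and a completers' analysis, and neither exempts safety. Item 20a does not mention safety by name, so its reach to adverse events is a literal reading and not an explicit instruction. Item 18b needs no such step, because it covers a leaver's data without distinction.

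**Conclusion.** The point holds as a faulty endpoint statement combined with conflicting analysis rules. It is certain that the visit sentence is wrong as written and contradicts both the definition before it and the UPDRS III primary outcome. It is also certain that items 18b and 19 disagree on the use of data from people who withdraw.

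The loss of harms from the analysis is a possibility that the text allows, not a stated plan. It arises if item 18b, or the completers' analysis in item 20a, is applied literally to adverse events. Its size and direction are unknown. The range of 0% to 12.5% per arm rests on an assumed zero to three early leavers with an event, no events among completers and no other leavers. The efficacy comparison is not affected by this point. The correction is worth making because it costs little and the arms are small.

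**What to change.** 1. In item 22, delete the sentence "The primary outcome is a four-month safety visit".
2. Align the abstract with the cumulative definition.
3. State the primary safety endpoint as the number of participants with at least one adverse event, and separately at least one serious adverse event, from first device use to the 4-month visit or last contact. Report it by arm in everyone who used a device at least once, whether or not they stopped.
4. In item 18b, exempt safety data from the exclusion, so that it agrees with the consent provision in item 19. In item 20a, say that the completers' analysis does not apply to adverse events.

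The cost is a few sentences, plus keeping or restoring the event records of early leavers in the analysis file. No treatment or stopping rule changes. By the dates under Trial status, follow-up may already be over. The definition can still be settled before the groups are revealed, which item 17b places after the outcome analyses.

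A fixed weekly adverse-event question in each participant's existing WeChat group, where "Within this group, daily treatment photos will be shared to facilitate supervision and identification of stimulation sites", would be an optional extra. It corrects no stated error and may suit only the later multi-center study.
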